### SA group

The environmental requirements, the acupuncture position, and the treatment frequency of the SA group will be consistent with those of the TA group. The protocol uses a specific blunt needle (30 × 25 mm, Huatuo, Suzhou, China). Acupuncturists will immobilize the translucent tube with double-sided adhesive on the same acupoints as those used in the TA group; then, the acupuncturists will pretend to insert the blunt needle through the tube and keep the needle standing vertically. The patients will feel a little stabbing pain; however, they are not likely to know that the needle did not prick their skin. The operational difference between TA and SA is shown as follows in Fig. 4.

**Fig. 4 Fig4:**
[figure not shown]
The operation of sham acupuncture. The sham acupuncture model is made up of the translucent tube, the double-sided adhesive, and the blunt needle which can keep the needle standing vertically without piercing into the skin

### MC group

Patients randomized to the MC group will be given aspirin enteric-coated tablets (100 mg qd po, Bayer) and atorvastatin calcium tablets (10 mg qd po, Pfizer) for antiplatelet aggregation as well as lipid-lowering effects. The drugs will be administered and provided to patients for free every week by the researchers. Once the patients forget to take pills or stop for personal reasons, researchers will record the detailed to individual situations. If patients are required to take other drugs for a long period due to illness, then the drug name, dosage, and frequency will be recorded.

## Outcome

Ultrasound and biochemical indicators will be used as outcome measures. The primary outcome consists of the total PV and the grey-scale median (GSM), and intima-media thickness (IMT), lipid levels, apolipoprotein A-IV level, platelet count (PLT), fibrinogen (FIB), and platelet aggregation rate (PAR) are the secondary outcomes. Biological specimens will be stored at − 80 °C after collection. All the biological specimens will be analysed in the current trial and for future use in ancillary studies.

### Primary outcome

Vessel plaque quantification (VPQ) is preferred for observing plaque morphological characteristics as a non-invasive assessment method [23]. The vessel plaque quantification technique has a substantial advantage over traditional two-dimensional ultrasound, which has been used for vascular event risk prediction. There are two aspects to be measured by the same sonologist: the total PV of the carotid artery on each side and the grey-scale median (GSM), which can indicate the average hardness of plaques proportionally [24, 25]. Both the PV and GSM will be assessed on weeks 0, 12, and 24 on each side.

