## Methods

### Study design

This is a three-arm randomized, parallel control clinical trial. The study objective is to evaluate the efficiency and reliability of acupuncture to relieve CAD. Three groups will be randomly established at a 1:1:1 ratio, including the TA group (receiving acupuncture therapy), the SA group (receiving sham acupuncture therapy), and the medication group (taking aspirin and statins). The study will enrol 105 individuals in total, 35 individuals in each group. The medication group is set for the positive control to evaluate the difference in the curative effect between acupuncture and drugs. At the same time, sham acupuncture group is set for placebo control to evaluate the clinical efficacy of acupuncture. The flowchart of this protocol can be found in Fig. 1.

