### Randomization

Baseline data of participants will be collected within 2 weeks and evaluated before random assignment. Participants will be assigned to the TA group, the MC group, or the SA group at a ratio of 1:1:1. To ensure the equality of random distribution, the generation of random sequences will be performed by the Acupuncture Research Institute, who will not participate in this study. Random numbers and grouping results will be saved in opaque envelopes by the staff who performed the randomization. All envelopes will be kept by staff who will not participate in the study. The research assistant will open the envelopes to assign them in the order in which they are registered.

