### Sample size

This is a three-arm study. In our search for previous studies of the effects of acupuncture on the carotid atherosclerotic plaque, it was found that most of the studies were two-arm studies of acupuncture versus drugs. There is a lack of high-quality clinical research. In addition, the effect of acupuncture exhibits a significant correlation between acupoints. Therefore, it is not appropriate to use the previous acupuncture clinical research literature data to estimate the sample size. Furthermore, this is a pilot study to guide future randomized controlled trials and to test the feasibility of the protocol. Considering that there are many clinical blood tests in the study, we will choose the clinical minimum sample size of 30 individuals for each group to reduce the burden of detection of the subjects. The maximum dropout rate within the intervention is expected to be approximately 15%. The total number of patients needed to be randomized is therefore 105 (35 for each group).

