### Statistical analysis

This study will use per-protocol (PP) and intention-to-treat (ITT) analysis principles. ITT will include all subjects who participated in at least one treatment, including participants who dropped out. Missing data for participants who dropped out will be supplemented with the most recent data. The PP principle will analyse all participants’ data that conform to the study protocol, and those of individuals who did not conform to the protocol will not be included.

The data will be analysed by professional statisticians with SPSS 20.0 software (IBM SPSS Statistics, IBM Corp, Somers, NY, USA). First, we will describe the baseline data, such as age, blood pressure, course of the disease, BMI, and sex, and compare the baseline data between the three groups. The continuous variables will be presented as the mean ± standard deviation (SD), and the categorical variables will be presented as the composition ratio and rate.

Continuous variables that conform to a normal distribution will be analysed by ANOVA, and the non-conforming data will be analysed using the rank sum test. Categorical variables will be analysed using the chi-square (*χ*^2^) test or Fisher’s exact test. The confidence interval (CI) will be estimated at 95%, and the significance level will be set at 0.05. A *P* value < 0.05 will be considered statistically significant. The adverse data will be recorded and analysed for the relationship with acupuncture. We will calculate the dropout rate and analyse the reasons for dropping out.

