### Comprehensive selection of outcome measures

Doppler ultrasound technology is an economical, simple, non-invasive detection method that is widely used for carotid atherosclerotic plaque and stenosis detection. The vessel plaque quantification technique used in this study can assess PV, plaque composition, and plaque remodelling structure.

The GSM value is an average evaluation of the plaque on one side of the carotid artery, which can effectively evaluate the components of the plaque. The lower the GSM value, the higher the lipid content in the plaque, and the higher the GSM value, the higher the calcium and fibre content in the plaque [24]. The GSM value of the plaque is related to plaque stability, and plaques with high lipid content usually have higher instability.

Lipid metabolism plays a key role in plaque elimination. HDL has anti-atherosclerosis effects, and its concentration is negatively correlated with the occurrence and severity of atherosclerosis. The main component of HDL is apolipoprotein A-I (70%), followed by apolipoprotein A-II and apolipoprotein A-IV. In this study, we will observe whether acupuncture plays an anti-atherosclerotic plaque role by regulating blood lipid levels.

In terms of coagulation-related indicators, most scientists believe that inflammation can stimulate the vascular endothelium to activate platelets and promote the binding of platelets to fibrinogen, thereby promoting arteriosclerotic thrombosis. Our previous study revealed that apolipoprotein A-IV is a new ligand for platelet GPIIβ/IIIα integrin, which competitively inhibits the binding of glycoprotein GPIIβ/IIIα to fibrinogen and inhibits platelet aggregation [27, 29]. In this study, platelet function will be used as an entry point to explore whether acupuncture can antagonize the binding of platelets to fibrinogen by changing the level of apolipoprotein A-IV, thereby reducing the PAR in blood and reducing the formation of plaque. Figure 5 shows the way in which acupuncture may affect apolipoprotein A-IV.

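### Up to eight unranked primary tests at 0.05, and a three-arm ANOVA that does not isolate acupuncture versus sham

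*Protocol article*

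**What the plan says.** All references are to the Protocol article.

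- **Outcomes.** The Outcome section lists PV and GSM together as primary. It gives neither precedence and does not say whether one or both must show an effect.
- **Sides and times.** Under Primary outcome, PV is defined separately for each carotid side, and "Both the PV and GSM will be assessed on weeks 0, 12, and 24 on each side". In the Discussion (Comprehensive selection of outcome measures), "The GSM value is an average evaluation of the plaque on one side of the carotid artery". No rule combines the two sides into one value per patient, and neither week 12 nor week 24 is called the main time point.
- **Test.** Statistical analysis assigns ANOVA to normally distributed continuous variables and a rank sum test to the rest. It adds that "the significance level will be set at 0.05" and that any P value below this counts as significant. No pair of arms is named.
- **Purpose of the arms.** Under Study design, MC is a positive control for comparing acupuncture with drugs, and the "sham acupuncture group is set for placebo control to evaluate the clinical efficacy of acupuncture". The two purposes are not ranked, and neither is linked to a test.
- **Status.** Sample size says "this is a pilot study to guide future randomized controlled trials and to test the feasibility of the protocol". The last paragraph of the Background nevertheless states a main objective that concerns how well acupuncture works on plaque.

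**The concern.** Two separate problems follow from the text.

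The first is the number of chances to succeed. With two unranked outcomes, two sides and two post-baseline visits, a significant result in any one cell could be reported as a positive primary result, and nothing written in advance says which cell counts.

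The second is a mismatch between the test and the question. A three-arm ANOVA asks whether the three means are all equal. The sham arm exists so that TA can be compared with SA. The protocol itself expects the drug arm to act on plaque: the Discussion credits statins with a plaque-stabilising effect and links GSM to stability. A significant ANOVA caused by MC alone, with TA no different from SA, is therefore foreseeable. At stake is whether a significant primary result would tell the next trial anything about acupuncture against sham.

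**Working it through.** **Inputs from the document.** Two primary outcomes (Outcome); two sides and two post-baseline visits, weeks 12 and 24 (Primary outcome); three arms at 1:1:1 (Randomization); 0.05 per test (Statistical analysis); 30 evaluable patients per arm and about 15% dropout (Sample size).

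**Inputs assumed.** Correlations between sides, visits and outcomes, and the size of any MC effect. The document gives none of these, so ranges are shown.

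**1. The plan's own figure.** No power or overall error rate is stated, so there is none to reproduce. The total of 105 is matched by 30 × 1.15 = 34.5, rounded up to 35 per arm, × 3 = 105. (Dividing instead, 30 / 0.85 = 35.3, gives 36 per arm and 108.) With 35 randomized, 35 × 0.85 = 29.75 remain, so 30 per arm is used below.

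**2. Number of possible primary tests.** 2 outcomes × 2 sides × 2 visits = 8.

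**3. Chance of at least one false positive, no effect in any arm, independent tests.** The formula is 1 − 0.95^k.

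- k = 2 (PV and GSM only): 1 − 0.95² = 9.75%
- k = 8: 1 − 0.95⁸ = 33.7%

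**4. The same with correlated endpoints.** Simulation of 3 arms × 30 patients × 8 normal endpoints, 20,000 runs, one three-arm ANOVA per endpoint at 0.05:

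| Correlation: sides | visits | outcomes | At least one P < 0.05 |
|---|---|---|---|
| 0 | 0 | 0 | 33% |
| 0.3 | 0.5 | 0 | 32% |
| 0.5 | 0.7 | 0.2 | 28% |
| 0.5 | 0.8 | 0.3 | 27% |
| 0.7 | 0.9 | 0.5 | 21% |

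Against a nominal 5%, 21% to 34% is roughly four to seven times too high.

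**5. A drug-arm effect with TA equal to SA.** Put the arm means at 0, 0 and d (in SD units), with MC at d. The grand mean is d/3, so the squared deviations sum to d²(1/9 + 1/9 + 4/9) = 2d²/3. The noncentrality is 30 × 2d²/3 = 20d², with 2 and 87 degrees of freedom.

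| Assumed MC shift d | Noncentrality | One ANOVA significant |
|---|---|---|
| 0.3 SD | 1.8 | 20% |
| 0.5 SD | 5.0 | 49% |
| 0.8 SD | 12.8 | 89% |

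In simulations of the same three settings, a direct TA versus SA t-test in one cell was significant 4.9%, 5.2% and 4.9% of the time, as it should be when the two arms do not differ.

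**6. After the fix.** One outcome, one patient-level value, one visit and one contrast give one test at 5%. Keeping PV and GSM as alternatives at 0.025 each gives 1 − 0.975² = 4.9%.

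**The case against.** The strongest reply has three parts.

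*This is a condensed article about a pilot, and no statistical analysis plan is shown.* Multiplicity rules, follow-up contrasts and the handling of sides are often left to that plan, so their absence alone is not a fault. This stands. The point does not rest on absence, however. It rests on what is written: two unranked primary outcomes, per-side definitions, a significance rule, and a named test that does not match the purpose given for the sham arm. The pilot label limits the consequences, but the main objective is still an efficacy one and P < 0.05 is still the criterion.

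*Eight is a maximum.* The sentence on weeks and sides is a measurement schedule. Separate testing of each cell is inferred from it and from an analysis described one variable at a time. This stands too, and is why the claim is worded as up to eight. The lower bound, two outcomes at one time on one summary, still gives about 10%.

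*An MC difference is not irrelevant.* Comparing acupuncture with drugs is a stated purpose, so a difference between TA and MC answers one of the trial's questions. What it does not answer is TA versus SA. Nor does the article say that a significant ANOVA will be read as proof of acupuncture's efficacy; the fault is that the test leaves this open.

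A reader might also infer any of the following, none of which the document supports:

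- that every pair of arms will be compared without adjustment in every cell (no pairwise procedure is named);
- that the two sides will be pooled as if they were independent patients (this is not stated);
- that patients with plaque on one side only will leave GSM undefined on the other (the inclusion criteria do not settle whether such patients enter).

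**Conclusion.** The concern holds in a limited form. As written, the plan allows up to eight primary tests at 0.05. If no arm has any effect, the chance of at least one false positive is at most about 34%, and 21–32% over the range of correlations assumed here; the two primary outcomes alone give about 10%. It would go too far to say that a chance finding is likely: all these figures are well below one half.

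Separately, the only named test does not isolate TA versus SA. With 30 per arm, TA equal to SA, and MC shifted by 0.3, 0.5 or 0.8 SD, one ANOVA is significant 20%, 49% or 89% of the time. Those shifts are assumptions; the document gives no effect size or SD from which to choose among them. The calculations also assume normal outcomes with equal variances.

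**What to change.** In the Outcome and Statistical analysis sections:

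1. Name TA minus SA, with its 95% confidence interval, as the primary contrast, and TA minus MC as secondary.
2. Define one value per patient over both sides, for example left plus right PV, and state the corresponding rule for GSM if it stays primary.
3. Name one primary time point, for example week 12, the end of treatment.
4. Either choose one primary outcome, or keep PV and GSM under a stated rule: both must succeed, or 0.025 for each.
5. Treat the other visit and side-specific results as secondary.

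An acceptable alternative is to declare all efficacy tests in this pilot exploratory and to report estimates with confidence intervals for planning the next trial. Which outcome leads, and how GSM is combined across sides, is for the sponsor to choose; what matters is that the choice is fixed before any comparison by arm is seen.

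The cost is wording. No new data are needed, and no stated power is contradicted, because the sample size has no power basis. The downside is that fewer results may be called significant.

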### Secondary outcomes

#### Regular carotid ultrasound

For diagnosing atherosclerosis, every participant will be required to undergo regular carotid ultrasound for screening before entry. Intima-media thickness (IMT) will be measured at study entry, exit, and follow-up. A prior study has documented that people with higher IMT are more likely to suffer from cardiovascular disease (CVD), especially stroke [26]. Aside from IMT, the maximum thickness of a single plaque, which is calculated by Crouse integration, will be measured throughout the study at each assessment.

#### Lipid level testing

As a previous study described, dyslipidaemia, such as high TGs and high total cholesterol (TC), usually occurs along with atherosclerotic plaques. Therefore, the modification of blood lipids, including TGs, TC, HDL, and LDL, seems to play a vital role in controlling the progression of atherosclerosis. Patients will undergo three blood tests to estimate their lipid level before and after the treatment, as well as after the follow-up period. The blood sample collection will be performed with the participants in a fasting state before 10 am.

#### Apolipoprotein A-IV testing

Apolipoprotein A-IV is a type of HDL that can activate LCAT and participate in the antidromic transport of TGs. Prior to the work of Xu et al. [27], apolipoprotein A-IV was considered a new-found ligand of αIIbβ3 integrin on platelets. In other words, apolipoprotein A-IV can antagonize the combination between platelets and fibrinogen. Consequently, the study will use apolipoprotein A-IV as one of the secondary outcomes to determine whether acupuncture could inhibit platelet aggregation by improving apolipoprotein A-IV levels in the blood.

#### Coagulation testing

Several coagulation-related measures are also involved in this protocol; these measures consist of platelet count (PLT), fibrinogen (FIB), and PAR. Thus far, platelet aggregation and hypercoagulability are regarded as the initial factors of atherothrombosis that can ultimately cause myocardial infarction or cerebrovascular accidents.

### Sample size

This is a three-arm study. In our search for previous studies of the effects of acupuncture on the carotid atherosclerotic plaque, it was found that most of the studies were two-arm studies of acupuncture versus drugs. There is a lack of high-quality clinical research. In addition, the effect of acupuncture exhibits a significant correlation between acupoints. Therefore, it is not appropriate to use the previous acupuncture clinical research literature data to estimate the sample size. Furthermore, this is a pilot study to guide future randomized controlled trials and to test the feasibility of the protocol. Considering that there are many clinical blood tests in the study, we will choose the clinical minimum sample size of 30 individuals for each group to reduce the burden of detection of the subjects. The maximum dropout rate within the intervention is expected to be approximately 15%. The total number of patients needed to be randomized is therefore 105 (35 for each group).

### Safety assessment

To reduce the risk of adverse events, firstly, acupuncturists should have years of work experience. Before the study begins, all acupuncturists need a unified training to standardize the acupuncture operation and increase the safety of acupuncture. Secondly, during the research process, the cardio-cerebrovascular doctor will evaluate the patient’s condition to ensure that the patients with severe cardio-cerebrovascular disease during the study period can be treated in time. During the treatment, the acupuncturist will also evaluate the subject’s condition to reduce the occurrence of adverse events. Finally, this study will be conducted in Guangdong Provincial Hospital of Traditional Chinese Medicine. The hospital has a strong medical level and ability to handle crisis events, which can guarantee the progress of this study. Acupuncture may cause some adverse reactions, such as bleeding, redness, fainting, and pain. All adverse events need to be recorded in common reporting format (CRF) tables. Adverse event records should include time, symptoms, extent, and their relationship with acupuncture. The investigator should handle and record adverse events. Serious adverse events should be reported to the Guangdong Provincial Hospital Ethics Committee. Participants who are unable to continue participating in the study due to adverse events will be excluded.

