## Intervention

The protocol design was based on previous clinical research and the classic theory of Chinese medicine. All operations adhered to the Standards for Reporting Interventions in Clinical Trials of Acupuncture (STRICTA) standard [21]. Acupoints applied in the RA and SA groups are the same as those listed in Table 1 and Fig. 3, according to the WHO Standard Acupuncture Locations guideline [22]. All acupuncturists who will take part in the research will be qualified to perform acupuncture with at least 5 years of study experience or 3 years of related work experience. Before implementation, all the researchers engaged in this study will participate in a unified training programme together. The groups will undergo the treatments separately twice per week for 24 treatments in total. In order to ensure the rights and interests of the patients and meet the ethical requirements, the subjects are allowed to use the treatment for diseases (such as cervical spondylosis, pain, insomnia, and fever) which are not closely related to atherosclerosis during the study period. It should be noted that the treatment received by the patients cannot interact with the drugs taken in the study, and the patients cannot receive any other acupuncture treatments so as not to interfere with the evaluation of the efficacy of the interventions included in the study.

**Table 1 Tab1:** Acupoints in both the TA group and the SA group

Name	Locations
*NEIGUAN* (PC6)	On the palmar side of the forearm, 2 in. superior to the transverse crease of the wrist, between the palmaris longus tendon and the radial wrist flexor tendon.
*RENYING* (ST9)	Lateral to the laryngeal prominence of the cervical region, the anterior margin of the sternocleidomastoid, at the fluctuation place of the common carotid artery.
*BAIHUI* (DU20)	On the median line of the head, 5 in. superior to the anterior hairline, at about the middle of the connecting line between both auricular tips.
*YINTANG* (EX-HN3)	At the middle between the two eyebrows on the forehead.
*YANGLINGQUAN* (GB34)	On the lateral side of the shank, in the depression anterior and inferior to the head of the fibula.

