### Data collection and management

This study will collect population data from eligible participants before the first treatment; these data include name, age, duration, occupation, blood pressure, sex, and body mass index (BMI). Drug and acupuncture adverse reactions will be recorded during the treatment and follow-up periods based on the reaction of the participants. At weeks 0, 12, and 24, data on carotid ultrasound, blood lipids, platelet aggregation, fibrinogen, platelet count, and apolipoprotein A-IV will be collected. The data collection will be performed by three staff members who will not take part in acupuncture treatment, index evaluation, statistical analysis, or grouping. The data collection and entry will be performed independently by two of the staff members and finalized by a third staff member. The main investigators, acupuncturist, sonographers, and laboratory staff will not be involved in data collection.

All data must be saved in paper with identification codes in seal, while electronic data is saved on the ResMan Research Manager of the Clinical Trial Management Public Platform, and photo formats are also named with identification codes to ensure authenticity and integrity. All data must be saved in paper, electronic, and photo formats to ensure authenticity and integrity. The data should be kept for at least 5 years after the article is published. A data monitoring committee was also set up in this study, composed of experts with good clinical research experience in the Department of Acupuncture of Guangdong Provincial Hospital of Traditional Chinese Medicine. Experts will regularly monitor research progress, data, participant management, distribution, and more. The committee is independent from the fund sponsor and has no conflicts of interest. Researchers who take charge in the data collection and entry will have access to the interim results and report to main investigators if necessary. Consequently, the main investigators will make the final decision to terminate the trial after discussion.

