### Selection of medication and placebo acupuncture method

There are different methods for the sham group based on acupuncture research, such as superficial skin acupuncture, non-acupoint acupuncture, and random acupoint acupuncture. According to the purpose of this study, we will adopt blunt needle acupuncture, which can avoid the effect of acupuncture epidermis therapy, and the design is more rigorous.

For drug selection, this study will use aspirin plus statins. The US 2014 AHA/ASA first-line prevention guidelines for stroke recommended that patients with asymptomatic carotid stenosis take aspirin or statin drugs [30]. Previous studies have suggested that the recommended dose of long-term aspirin is 75–150 mg/day. Most participants in this study are mild symptomatic carotid atherosclerotic plaque patients, which is consistent with the primary prevention of stroke. Based on the opinions of the Ethics Committee of the Guangdong Provincial Hospital of Traditional Chinese Medicine and patient’s risk factors, the dose of aspirin was adjusted to 100 mg/day. Statins exert beneficial effects for arteriosclerosis patients by reducing blood lipids and stabilizing plaques. According to the systematic analysis of the effects of different doses of atorvastatin on Chinese carotid artery stenosis (CAS) patients, patients taking 10 mg/day suffered fewer side effects, such as transverse muscle dissolution and elevated transaminase, while the treatment effect showed no significant difference. From an ethical point of view, the clinical dose of atorvastatin used in this trial is 10 mg/day after discussion.

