### The basis of treatment sequence selection

Referring to the prior related research and taking into account patient compliance and other factors [31–33], the course of treatment is set at 12 weeks with 2 treatments per week for 24 treatments in total. Participants must complete at least 80% of treatments to be considered compliant. Patients will be followed up for 12 weeks after finishing treatment.

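### Adverse events are recorded without a common enquiry schedule, and scheduled contact is about twice as frequent in the acupuncture and sham arms as in the medication arm, so event counts against medication are open to unequal detection

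*Protocol article*

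**What the plan says.** On contact during treatment, the Intervention section states: "The groups will undergo the treatments separately twice per week for 24 treatments in total". The Discussion repeats the figure: "the course of treatment is set at 12 weeks with 2 treatments per week for 24 treatments in total". For sham, "the treatment frequency of the SA group will be consistent with those of the TA group". For medication, the MC group section states: "The drugs will be administered and provided to patients for free every week by the researchers". The items it says researchers will note are missed or stopped pills and other long-term drugs. It attaches no adverse-event enquiry to the hand-out.

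On observation of harms, Safety assessment has two provisions. One is not limited to an arm: "during the research process, the cardio-cerebrovascular doctor will evaluate" the patient, so that severe cardio-cerebrovascular disease is treated in time. The other is tied to the sessions: "During the treatment, the acupuncturist will also evaluate" the participant's condition, with the stated aim of making adverse events less likely.

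On recording, Data collection and management states: "Drug and acupuncture adverse reactions will be recorded during the treatment and follow-up periods based on the reaction of the participants". Recruitment adds a WeChat group through which every participant can report events to doctors whenever they wish. The article states no fixed set of questions or common timetable for asking about events.

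**The concern.** How many events a trial records depends on how often, and how actively, someone looks. Here one kind of arm is seen by a treating clinician twice a week, and the other collects tablets once a week from researchers whose stated task there is adherence and co-medication. Everything else relies on participants to speak up.

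The Abstract presents acupuncture as a therapy expected to be safe, and the Background and Discussion set it against drugs whose side effects are described as hard to avoid. Readers will therefore put the event counts of the three arms side by side. If fewer transient complaints are noticed in MC, the drugs look better tolerated than they are relative to acupuncture, and a true advantage of acupuncture could be hidden. As this is a pilot meant to guide larger trials, its event rates are likely to be carried forward. Later analysis cannot recover events that nobody asked about.

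**Working it through.** **Contacts.** The plan's own figure reproduces: 12 weeks × 2 per week = 24 sessions in TA, and the same in SA. For MC, 12 weeks × 1 hand-out per week = 12 (derived; the article gives no count). The ratio is 24/12 = 2 for either acupuncture arm against MC, and 24/24 = 1 for TA against SA.

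Read literally, the Intervention sentence on twice-weekly treatment covers all groups. The MC section, however, gives weekly supply of daily tablets, and no acupuncturist sees these patients, so 12 is the natural reading.

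**From contacts to recorded events.** The documents give neither event durations nor reporting rates, so both are assumed here.

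- D: days an event lasts, with onset at random relative to contacts.
- Contacts evenly spaced: every 3.5 days in TA and SA, every 7 days in MC.
- An event present at a contact is noted. Of the events not seen, a share q is recovered later by recall or self-report.
- True event rates are equal in all arms.

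Probability of being recorded:

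- TA or SA: A = a + (1 − a)q, with a = min(1, D/3.5)
- MC: M = m + (1 − m)q, with m = min(1, D/7)

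Worked case, D = 2 and q = 0.5: a = 2/3.5 = 0.571 and m = 2/7 = 0.286. Then A = 0.571 + 0.429 × 0.5 = 0.786, M = 0.286 + 0.714 × 0.5 = 0.643, and A/M = 1.22.

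Ratio of recorded events, acupuncture arm to MC:

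| D (days) | a | m | q = 0 | q = 0.5 | q = 0.8 |
|---|---|---|---|---|---|
| 1 | 0.286 | 0.143 | 2.0 | 1.125 | 1.03 |
| 2 | 0.571 | 0.286 | 2.0 | 1.22 | 1.07 |
| 3.5 | 1 | 0.5 | 2.0 | 1.33 | 1.11 |
| 5 | 1 | 0.714 | 1.4 | 1.17 | 1.06 |
| 7 or more | 1 | 1 | 1.0 | 1.0 | 1.0 |

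With q = 1 (everything reported eventually), A = M = 1 and the ratio is 1.0 for every duration. The possible distortion therefore runs from none to twofold, always towards more recorded events in TA and SA.

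The model suits events unconnected with the session. Reactions caused by needling arise in front of the acupuncturist, so a higher count of those partly reflects exposure, not surveillance.

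**The case against.** The strongest reply is that the sessions are not the recording route. The acupuncturist's evaluation is described as prevention, Safety assessment gives recording to the investigator, and Data collection and management keeps the acupuncturist out of data collection. This stands in part: 24 sessions are not 24 formal ascertainments. But each is a face-to-face check at which a complaint can surface and be passed on, and every adverse event has to be recorded.

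Secondly, a reader might infer that MC participants are observed only when they collect tablets. The documents do not support that. WeChat reporting, the cardio-cerebrovascular doctor and the assessments at weeks 0, 12 and 24 serve all arms. These provisions narrow the gap without closing it. WeChat relies on self-report, the doctor's evaluation has no stated frequency and is aimed at severe disease, and the common visits are 12 weeks apart.

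Thirdly, no drug-versus-acupuncture harm test is specified. The only stated adverse-event analysis concerns the relationship with acupuncture, and Study design includes MC to compare curative effect. This is correct, and it limits the point to descriptive comparisons that the rationale invites.

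Finally, q = 0 is extreme: a patient seen weekly can mention a symptom that has passed. That too is right. At q = 0.8 the ratio is 1.03 to 1.11 for events of 1 to 3.5 days.

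**Conclusion.** The concern holds in a limited form. Scheduled contact is 24 against about 12, a treating clinician's evaluation is written only for acupuncture sessions, and recording is otherwise passive. Comparisons of recorded events with MC are therefore open to ascertainment bias, between none and about twofold on the assumptions above. TA versus SA is not affected by contact frequency, and no efficacy comparison is touched.

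Three stronger conclusions are tempting and should not be drawn.

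- That the comparison is biased by a known amount. The size rests wholly on assumed durations and recall, and can be nil.
- That drug harms are missed in the laboratory. The Discussion names atorvastatin side effects, "such as transverse muscle dissolution and elevated transaminase", and the data listed for weeks 0, 12 and 24 include no test for them. But that list is in a condensed article whose schedule figure is not shown, so absence there does not show absence from the full protocol.
- That dropout for adverse reactions is distorted in the same way. The dropout criterion concerns severe reactions that prevent completion of the course, and these come to light however often the patient is seen.

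**What to change.** Ask all three arms the same short adverse-event question list, in the same words, on the same weekly schedule: at the drug hand-out in MC and at one fixed session per week in TA and SA. Ask it again at weeks 12 and 24. Base any between-arm description of harms on these solicited answers. List separately the events noted only at other sessions or through WeChat.

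The cost is a page in the case report form and slightly more form-filling, at contacts that already take place. It needs no extra visits and leaves the sample size unchanged.

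The main drawback is timing. Trial status reports that 42 of the planned 105 (42/105 = 40%) had participated by October 2019, and these were followed by the existing method. Their events, and those of anyone else treated before the change, should be reported separately and not pooled with the solicited data.
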